## Methods/design

### Design

This is a three-site phase IIb randomised double-blindplacebo-controlledparallel-group trial. Participants will be recruited across three sites (*N* = 180; 60 per site) and randomly assigned (1:1) to receive either oral NAC 2400 mg daily or the placebo, for 12 weeks. Weekly assessments throughout the 12-week medication phase will be used to assess outcomes. The trial flow diagram is presented in Fig. 1. The trial protocol was developed in accordance with the Standard Protocol Items: Recommendations for Intervention Trials (SPIRIT) Statement (see Additional file 1 for the SPIRIT checklist).

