### Randomisation and blinding

Participants are randomised to the treatment or placebo arms in a 1:1 ratio using a permuted block randomisation schedule with variable block sizes, stratified by site (Melbourne, Geelong or Wollongong), gender (male or female) and main route of methamphetamine administration in the month prior to recruitment (injecting or not injecting). The randomisation sequence was generated a priori using an in-house custom program written by WL. A random seed, assigned by the data and safety monitoring board (DSMB) statistician, was used to generate the final randomisation schedule using this program. Allocation to treatment condition (placebo vs. NAC) is based on the participant’s unique study identifier, this being assigned by trial staff sequentially within each stratum on randomisation.

All trial staff, the trial statistician (WL) and investigators are blind to treatment allocation. The randomisation schedule is held by the trial site pharmacy and the DSMB statistician. Allocation to trial arm is done by the trial pharmacist according to the randomisation schedule (provided by the DSMB statistician) using the unique study identifier provided by the trial staff. Packaging is identical to conceal treatment allocation. A removable adhesive label indicates whether the medication is placebo or NAC.

Unblinding is done at the discretion of the DSMB, the trial investigators or the treating medical physician in a medical emergency. Trial investigators can unblind individual participants via a password-protected online portal.

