#### Efficacy analysis

All tests will be two-sided with significance set at *p* < .025 for each of the two primary endpoints and *p* < .01 for each of the secondary endpoints. Significance for all other tests will be set at *p* < .05. The analyses will be conducted blind to condition.

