##### Analysis of secondary outcomes

Analysis of secondary outcomes will be based on a modified intention-to-treat dataset that includes only participants who completed assessment 0 and at least one follow-up assessment (i.e., assessments 1–12). The effect of NAC on each secondary outcome will be tested using a baseline (assessment 0) vs. medication phase (assessments 1–12) by treatment condition (NAC vs. placebo) interaction.

All effects will be tested with mixed effects models with repeated measures for each measurement time point. Heterogeneity in variance and treatment effect between sites will be tested for by seeing whether the model fit is significantly improved by including a random intercept for site and a random coefficient for the main effect by site, respectively. If no significant heterogeneity is found, the more parsimonious model will be retained. Missing data will be imputed using multiple imputation by chained equations implemented in Stata in the analysis of the primary outcomes only. Final details of the analysis, including methods of imputation and covariates, will be outlined in a statistical analysis plan prior to unblinding of the data. An additional statistical plan for a health economic evaluation will be developed prior to undertaking any such analysis.

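### Site terms in every efficacy model are chosen by an unreliable significance test on three sites; keep site as a fixed effect and report treatment by site descriptively

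*Protocol article*

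**What the plan says.** The rule is in the protocol article under Analysis of secondary outcomes, but its scope is wider than that heading: "All effects will be tested with mixed effects models with repeated measures for each measurement time point". Heterogeneity in variance and in treatment effect between sites is judged by whether "model fit is significantly improved by including a random intercept for site and a random coefficient for the main effect by site". If it is not, "If no significant heterogeneity is found, the more parsimonious model will be retained".

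The Design section gives three sites with 60 participants each. Under Randomisation and blinding, allocation is "stratified by site (Melbourne, Geelong or Wollongong), gender (male or female) and main route of methamphetamine administration", so site is a design stratum. The level for the heterogeneity tests is not given separately and falls under the general sentence in Efficacy analysis: "Significance for all other tests will be set at *p* < .05". Each primary outcome is tested two-sided at 0.025. Covariates and imputation methods are left to the SAP; the site rule is not.

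**The concern.** The rule lets a test on three sites decide which model produces the primary result. It can go wrong in two ways.

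- **The random treatment coefficient.** If treatment effects do differ between sites, a 2-df test will usually miss it, and the plan then proceeds as if homogeneity had been shown. If the coefficient is retained, rightly or by chance, the standard error of the treatment effect comes from the spread of three site differences.
- **The random intercept.** If it is dropped and the SAP adds no site covariate, a randomisation stratum leaves the model.

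At stake are the width of the primary confidence interval and the power of the trial. The first route is much the more serious.

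**Working it through.** **Inputs from the protocol article.** Three sites; n = 60 per site, or 48 after 20% attrition (72/0.80 = 90 per arm reproduces); 1:1 allocation; target difference 6.0 - 3.5 = 2.5 days per month; SDs 6.7 and 6.9, pooled √((6.7² + 6.9²)/2) = 6.80; test level 0.05; primary level 0.025 two-sided. The article gives no figure for the site test, so there is none to reproduce.

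**Assumptions not in the article.** Site ICC 0.01 to 0.10. Between-site treatment SD τ of 1.25 or 2.5 days. Residual SD σ of 4.5 to 6.8 days, the lower values allowing for averaging over three follow-ups and baseline adjustment. Equal sites, a normal outcome, z-based tests. The saliva outcome is binary, so the figures are only indicative for it.

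**Precision on 2 df.** The 95% range for a between-site SD, relative to its estimate, runs from √(2/7.378) = 0.52 to √(2/0.0506) = 6.28.

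**Random intercept.** The between-site mean square is inflated by 1 + θ, with θ = n·ICC/(1 - ICC). For ICC 0.05 and n = 60, θ = 60 × 0.05/0.95 = 3.16. Chance that a REML likelihood-ratio test with the boundary reference keeps the term:

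| ICC | 60 per site | 48 per site |
|---|---|---|
| 0.01 | 10% | 9% |
| 0.02 | 19% | 16% |
| 0.05 | 41% | 35% |
| 0.10 | 62% | 56% |

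At zero heterogeneity the true size is about 2.6% (1.2% with an ordinary 1-df chi-square), not 5%.

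**Random treatment coefficient.** Here θ = nτ²/(4σ²). For n = 60, τ = 1.25, σ = 5.0: 60 × 1.5625/100 = 0.94, and the term is detected in 15% of trials. Over σ from 4.5 to 6.8 and 48 to 60 per site, detection is 8-18% at τ = 1.25 and 25-52% at τ = 2.5, a spread as large as the target effect.

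**The whole rule against fixed site effects (σ = 5.0).**

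| True τ | Per site | Power, rule | Power, fixed site |
|---|---|---|---|
| 0 | 60 | about 84.5% | about 86% |
| 0 | 48 | about 75.5% | about 77% |
| 1.25 | 60 | 69% | 78% |

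At τ = 0 the type I error of the rule is 0.025-0.026. Chance retention of the coefficient accounts for nearly all of the small loss there: 0.027 × (0.86 - 0.11) = 0.020. Dropping the intercept therefore adds very little.

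**Days of use.** This outcome is tested as baseline versus medication phase by arm, a within-person contrast. In simulated complete data with site shifts of -10, 0 and +10 percentage points and a participant random intercept, the interaction estimate was the same with and without fixed site, and the standard errors agreed (2.7267 and 2.7267 in one trial). Saliva has no baseline sample (Table 1) and is tested as a main effect, so there a site shift does not cancel.

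**What fixed site effects mean if τ > 0.** For the average effect over these three sites the test keeps its level. For the mean of a wider population of sites it does not. With τ = 1.25 and n = 60, τ²/3 = 0.521 and the sampling variance is 4 × 25/180 = 0.556. The z statistic is inflated by √(1 + 0.521/0.556) = 1.39, and 2.24/1.39 = 1.61 gives about 11% two-sided. The rule does little better: it drops the coefficient in 85% of such trials, and 0.85 × 0.107 = 0.091.

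**The case against.** The strongest reply has four parts.

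- **The rule is prespecified and run blind to condition.** That limits deliberate steering. It does not remove the effect of selecting a model from outcome data.
- **Dropping the intercept is nearly harmless.** This stands. The term goes mainly when the estimated site variance is small, and for days of use it hardly enters the treatment contrast. A reader might infer that standard errors are generally too large or that type I error is inflated. With no treatment-by-site variation the figures show neither to any material degree.
- **Covariates are deferred to the SAP.** This stands in part. A fixed site term there is neither promised nor excluded, so one cannot say that site will be absent. The deferral does not undo the stated pretest, and if site were already a fixed covariate, testing a random intercept for it would be redundant. Sex and injecting route are untouched by the rule, so their absence from the article is no fault.
- **Random site effects suit an intervention meant for wide use.** The choice of target is legitimate, but three sites cannot support it, and the pretest does not deliver it (about 9% rejection above).

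Two stronger readings are also tempting. One is that the test has almost no power and cannot work; at ICC 0.10 it keeps the intercept in 56-62% of trials, so it is unreliable rather than inoperable. The other is that the critical value becomes 6.21 instead of 2.24; that needs both retention of the coefficient and a 2-df reference, and the article names no reference distribution.

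**Conclusion.** The point holds as a recommendation to change the analysis; it is not a fatal flaw. The pretest is uninformative on three sites, and its main danger is the random treatment coefficient. That coefficient is missed in more than 80% of trials when τ is half the target effect and in about half or more when τ equals it, and it is very costly to power when retained. The loss is about 1.5 to 2 points with no true heterogeneity and about 9 points (78% to 69%) at τ = 1.25.

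The 9-point gap needs care: it rests on assumed values of τ and σ, and part of it reflects that fixed site effects answer a question about these three sites only. The intercept half of the rule is a minor matter, relevant mainly to saliva.

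**What to change.** Before unblinding, state in the SAP, and correct in the protocol, that:

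1. The heterogeneity pretest and both random site terms are removed from all efficacy models.
2. Site is a fixed effect in every efficacy model regardless of significance, preferably with the other two randomisation strata (sex and injecting route).
3. Treatment effects by site, with confidence intervals, are reported from a fixed site-by-arm interaction for saliva and a site-by-arm-by-phase interaction for days of use. This analysis is descriptive and does not alter the primary model. For days of use the treatment effect is the phase-by-arm interaction, so a site coefficient on a main effect, read literally, would not describe it.

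The cost is a change of wording and four main-effect parameters (two for site, one each for sex and route). Inference is then conditional on these three sites, and the SAP should say so.

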## Discussion

The N-ICE trial is the first randomised controlled trial to assess the efficacy of NAC as a pharmacotherapy for methamphetamine dependence. It will test whether NAC can produce a clinically meaningful reduction in methamphetamine use. It will assess whether there are any beneficial effects of NAC on related clinical endpoints, including psychiatric symptoms, and it will document adherence to NAC and the safety profile of NAC as a take-home medication in this population. Thus, the trial will improve our understanding of the potential utility of NAC in clinical practice to reduce methamphetamine use.

One clear potential benefit of NAC, if it is found to be safe and effective, is that it can be administered as a take-home medication, making it a potentially scalable and cost-effective treatment option. A significant impediment to the benefits of NAC, or any other take-home medication, would be poor compliance with dosing regimens. Thus, we are using electronic monitoring (eCAP™) to record the time and date of each occasion a bottle is opened to provide an objective measure of adherence. Electronic monitoring through devices such as eCAP™ is a relatively recent technological development [52] that has not yet been widely adopted in medication trials for illicit substance use. This technology will provide important data on the viability of prescribing take-home medications in illicit substance-using populations and it will also allow us to assess the implications of sub-optimal dosing on treatment effects and safety in this population.

Novel aspects of our trial procedures are the direct community engagement strategy to recruit participants and the outreach methods for follow-up assessments within the community, in so far as these are practical and safe. We have taken this approach because most people who are dependent on methamphetamine do not engage with specialist drug treatment services [53], and this has made recruitment to and retention in stimulant pharmacotherapy trials difficult [54]. Rather than relying on recruiting patients from existing clinical services and requiring that trial participants come to fixed sites for treatment, we use well-honed fieldwork methods that have been successfully applied in survey and cohort research involving people who use methamphetamine [42, 50, 55]. We hope that the implementation of these outreach methods within the clinical trial framework will increase engagement with consumers and improve retention.

A challenge that we faced in developing this trial protocol was the lack of standardised and readily available evidence-based treatment options for methamphetamine dependence. This precluded a treatment comparison arm or the provision of treatment as usual to trial participants. Instead, we provide all participants with a form of minimal intervention (an information booklet) and referral information for health services, which they are free to access throughout the trial period. To counter the risk of bias from concomitant treatment, we record all concomitant medications and psychosocial treatments for substance use and other mental health problems. We will compare treatment arms on these exposures and, where differences exist, we will adjust for these in the main analysis.

In summary, this trial is important because it tests a novel, affordable, available and tolerable non-agonist pharmacotherapy option for methamphetamine dependence, which, if effective, has the potential to be a much-needed, cost-effective and scalable treatment option for this population. NAC has the potential to be prescribed by primary health-care providers as a take-home medication and used as an adjunct to existing drug treatments. The lack of patent restrictions and its current availability as a prescription medication and dietary supplement will facilitate its uptake. Given the lack of approved medications currently available for managing methamphetamine dependence [3–5] and the challenges involved in translating effective psychological interventions into practice settings [56], the discovery of a safe and effective pharmacotherapy would fill an important gap in treatment options for methamphetamine use.

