### Setting and study population

Participants are being recruited via outpatient settings in Melbourne (Turning Point and Eastern Health), Geelong (Barwon Health) and Wollongong (Illawarra Drug and Alcohol Service) in Australia. All participants are volunteers. They provide written informed consent prior to participation (see Additional file 2 for the participant information sheet and consent form). Inclusion criteria are that participants must be aged 18–60 years, meet DSM-IV criteria for methamphetamine dependence, be seeking to reduce their methamphetamine use but are not currently undergoing substance use treatment (including pharmacotherapy for substance use disorders), are not in need of acute care for psychiatric or other medical conditions, do not have a primary psychotic disorder, are able and willing to comply with the trial protocol, and have no contraindications for NAC. Contraindications for receiving the trial medication include: previous hypersensitivity to NAC; use of medications containing NAC or thought to be hazardous if taken with NAC (e.g. carbamazepine and nitroglycerin); a known or suspected active systemic medical disorder including cancer or other medical condition that may exacerbate the risk of AEs from NAC (recent gastrointestinal ulcers or renal stones, epilepsy or history of seizures, asthma or atopy); and, surgery within the past 28 days. Further, participants must not be pregnant (confirmed at the eligibility assessment), lactating or planning to fall pregnant during the trial.

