#### Recruitment and screening

Participants are recruited through advertisements (e.g., Facebook, media activity, and flyers in needle and syringe programs) and word of mouth. They are screened by phone. Potentially eligible participants are consented by trial staff and then undergo a face-to-face eligibility assessment (1.5 to 2 h in total) to confirm their eligibility and to obtain information on demographics, drug use and psychiatric history. All participants undergo a medical assessment to confirm further their eligibility prior to randomisation. Randomisation must occur within 28 days of eligibility being confirmed. Eligible participants are provided with a list of local health service providers and are free to access drug treatment and other health services during the trial. Ineligible participants are offered referral to local alcohol and other drug services.

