#### Concomitant treatments

All medications, including supplements, taken during the trial and all treatments related to either substance use or other mental health conditions received during the trial will be recorded on a template adapted from the National Institutes of Health’s concomitant medications form [39].

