##### Analysis of primary outcomes

Intention-to-treat analyses will be conducted for the primary outcomes. The effect of the trial medication on days of methamphetamine use (percentage of days used in the past 28 days) will be tested using a baseline (assessment 0) vs. medication phase (three repeats: assessments 4, 8 and 12) by treatment condition (NAC vs. placebo). Unobserved days (e.g., due to hospitalisation or incarceration) will be censored. The effect of NAC on methamphetamine-positive saliva will be tested using a main effect for treatment condition (NAC vs. placebo) on saliva test results (positive vs. negative) from assessments 1–12 (12 repeats).

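### The main analysis is to be adjusted for concomitant treatment taken up during the trial whenever the arms differ on it, so where NAC affects uptake the primary estimate is no longer the effect of assignment

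*Protocol article*

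**What the plan says.** All references are to the protocol article.

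- **Adjustment rule (Discussion, on the lack of a standard comparator treatment).** The authors state that "we record all concomitant medications and psychosocial treatments for substance use and other mental health problems", and continue: "We will compare treatment arms on these exposures and, where differences exist, we will adjust for these in the main analysis". The stated purpose is to counter bias from concomitant treatment.
- **When the exposures occur (Concomitant treatments).** The record covers "All medications, including supplements, taken during the trial" and "all treatments related to either substance use or other mental health conditions received during the trial".
- **Access (Recruitment and screening; Setting and study population).** Participants "are free to access drug treatment and other health services during the trial". At entry they "are not currently undergoing substance use treatment", so treatment for substance use will normally have started after entry.
- **Measurement (Table 1).** Concomitant medications and treatments are recorded at assessment 0 and at each of assessments 1 to 12.
- **Primary analysis (Analysis of primary outcomes).** "Intention-to-treat analyses will be conducted for the primary outcomes".
- **Blinding and covariates.** Efficacy analysis says the analyses are done blind to condition. Analysis of secondary outcomes leaves final covariates to a statistical analysis plan, which is not shown.

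**The concern.** Randomisation makes the arms comparable at baseline. What happens afterwards, including who seeks counselling or starts another medication, can be a result of the assigned treatment. Aims and hypotheses expects NAC to reduce use, craving, withdrawal and psychiatric symptoms, and each of these could change who seeks help.

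If NAC changes uptake, adjusting for uptake does one of two things. It removes or adds the part of the effect that runs through uptake (a mediator), or it links assignment to an unmeasured cause of both uptake and use, such as severity (a collider). The adjusted coefficient is then not the effect of being assigned NAC.

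The trigger makes this worse. Adjustment applies only where the arms differ, so it applies most often when NAC has shifted uptake, which is when it is least valid. No criterion for a difference is given, so the covariates of the primary model depend on the trial data.

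**Working it through.** The plan gives no figure for this rule, no uptake rate and no estimate of what concomitant treatment does. The sample-size inputs are the plan's; everything about uptake is assumed.

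**Inputs from Sample size estimation and Efficacy analysis**
- Difference: 6.0 − 3.5 = 2.5 days per month.
- SD: √[(6.7² + 6.9²)/2] = 6.80.
- Evaluable per arm: 90 × 0.8 = 72, as stated.
- Two-sided alpha: 0.05/2 = 0.025 per primary outcome.

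The point does not rest on the stated 80% power, and these inputs cannot confirm or refute it. A single-measure comparison gives 48.6%. The mean of three repeats gives 81.0% at a within-person correlation of 0.25, but the plan states no correlation.

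**Scenario 1: uptake follows early use**

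Assumptions: true effect 2.5 days; within-person correlation 0.5; about 30% uptake on placebo; log-odds of uptake rising by 0.7 or 1.5 per SD of month-1 use. Mean medication-phase use is regressed on arm and baseline, and uptake is added only if a two-proportion test gives p < 0.05.

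Check on the set-up: with one baseline and three repeats the variance factor is (1 + 2 × 0.5)/3 − 0.5² = 0.417, and the analytic power is 88.0%. The simulated unadjusted power below agrees.

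| | Log-odds 0.7 | Log-odds 1.5 |
|---|---|---|
| Trials in which the rule triggers | about 10% | about 19% to 20% |
| All trials: unadjusted → under the rule | 2.48 → 2.45 days | 2.51 → 2.41 days |
| All trials: power | 86.7% → 85.6% | 87.8% → 85.2% |
| Triggered trials only: unadjusted → adjusted | 2.70 → 2.42 days | 2.83 → 2.23 days |

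- Average loss over all trials: 0.03/2.48 = 1.2% and 0.10/2.51 = 4.0%.
- Loss in triggered trials, against the unadjusted estimate: 0.28/2.70 = 10.4% and 0.60/2.83 = 21.2%.
- Loss in triggered trials, against the true 2.5 days: 0.08/2.5 = 3.2% and 0.27/2.5 = 10.8%. The unadjusted estimate in these trials is itself above 2.5, because selecting on an uptake difference selects large effects.
- Type I error under the rule with no true effect: 0.024 to 0.028.

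**Scenario 2: NAC shifts uptake, and concomitant treatment lowers use by 3 days**

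Total effect = direct effect + (−3) × (change in uptake). The adjusted model returns the direct effect only.
- Uptake up from 30% to 50%: −1.9 − 3 × 0.20 = −2.5 in total, but −1.9 adjusted. Single-measure power is 47% unadjusted and 31% under the rule, which triggers in 71% of trials.
- Uptake down from 30% to 15%: −2.95 − 3 × (−0.15) = −2.5 in total, but about −3.0 adjusted. Single-measure power is 49% unadjusted and 60% under the rule, which triggers in 57% of trials.

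**Scenario 3: NAC does not affect use but shifts uptake, and unmeasured severity drives both**

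Assumptions: severity raises the log-odds of uptake by 1.5 per SD and use by 4 days per SD; NAC shifts the log-odds of uptake by +0.85 or −0.88.
- Unadjusted estimates: −0.01 and −0.02 days, so close to zero.
- Adjusted estimates: −0.63 and +0.54 days.
- Type I error: 0.050 and 0.040 if always adjusted; 0.033 and 0.030 under the rule.
- With 2,000 trials the simulation standard error at 0.025 is √(0.025 × 0.975/2000) = 0.0035, so the excess under the rule is small and imprecisely estimated.

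**Scenario 4: NAC does not affect uptake, so any difference is chance**

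The average estimates with and without adjustment agree to about 0.01 day, type I error is about 0.025, and the rule triggers in 5% to 6% of trials.

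**The case against.** Several objections have force.

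- **The rule is one sentence in the Discussion, and covariates are left to the analysis plan.** That plan may demote or drop the adjustment. However, the article does not leave this point open: it states a rule and attaches it to the main analysis. A plan that follows it carries the problem; a plan that departs from it needs to say so.
- **Analyses are blind to condition.** This stands against any suggestion that covariates would be picked with knowledge of which arm is NAC, because coded arms can be compared without unblinding. It does not remove the bias, which arises whoever runs the model.
- **Some exposures are baseline.** Table 1 records them at assessment 0, and entry bars current treatment for substance use but not every other medication. Adjusting for assessment 0 values would be harmless. The Discussion sentence does not limit itself to those values.
- **The effect may be small.** This stands for Scenario 1 and for chance imbalance.

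A reader might infer that the analysis is not intention-to-treat at all. The documents do not support that: the rule excludes nobody and moves nobody between arms, and follow-up continues after medication is stopped for those who remain consented. What changes is the quantity estimated. A reader might also take the 10% to 21% loss as the expected effect of the rule. It describes only the minority of Scenario 1 trials in which the rule triggers.

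**Conclusion.** The concern holds in limited form. The stated rule lets the primary model condition on a variable that NAC can affect, and does so depending on the observed difference between arms. Where NAC does shift uptake, the primary estimate is not the effect of assignment.

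Size and direction cannot be fixed from the documents. Under the assumptions above:
- if uptake follows early use, there is an average attenuation of about 1% to 4% and a loss of 1 to 3 points of power, with type I error near 0.025;
- if NAC shifts uptake by other routes, the adjusted estimate is off by about 0.5 to 0.6 days in either direction, and by less on average under the rule because it does not always trigger;
- if imbalance is due to chance, there is no average bias.

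It would therefore be too strong to say that the rule will bias the result; it can. These figures concern days of use. The saliva outcome was not simulated, but the same reasoning applies to it, since the rule names the main analysis without exception.

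**What to change.** Replace the Discussion sentence, through the statistical analysis plan or a protocol clarification, with three statements:

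1. The primary models include no post-randomisation covariate. Covariates are limited to baseline and stratification variables.
2. Concomitant medication and treatment are tabulated by arm.
3. Any adjustment for concomitant treatment is confined to one prespecified supplementary analysis, labelled as such, which says what effect it estimates.

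If the analysis plan already does this, it should state that it supersedes the Discussion sentence. The change should be dated before the arms are compared on these exposures. It costs a few lines of text and needs no extra data or participants and no change to sample size or alpha.
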